# Effect of high-protein vs. high-fat snacks before lunch on glycemic variability in prediabetes: A study protocol for a randomized controlled trial

**DOI:** 10.3389/fnut.2022.925870

**Published:** 2022-07-19

**Keywords:** glycemic variability, pre-meal, snack, high-protein, high-fat, randomized controlled trial

## Abstract

**Background:**

China has the largest number of patients with Type 2 Diabetes Mellitus (T2DM), and it tends to increasingly grow in the future, putting an enormous burden on disease control and prevention in China. While glycemic variability (GV) came to be an important indicator of blood glucose control in diabetic patients, studies suggested that premeal snacks may help blood glucose control, but there are still some problems to be researched. Therefore, we designed this trial to evaluate which kind of premeal snacks would lead to better effects on GV under two diet patterns in pre-diabetes subjects and to evaluate assessments of acceptability and compliance, behavior, and metabolism changes in individuals will be described.

**Methods and analysis:**

The study is a single-center, open-label, multiparallel group, randomized controlled trial. A total of 32 male and female volunteers will be randomized into 4 groups in a single allocated ratio of soy milk (powder) snack, milk (powder) snack, almonds snack, and placebo control with 250 ml of water taken 30 min before lunch, respectively. The study consists of two intervention periods over 11 days. The first intervention period under habitual diet conditions from D3 to D6 (4 days), during which all subjects are asked to maintain their habitual eating and daily activities similar to the run-in period. The second intervention consists of prelunch snacks with standard meals. We will examine both the effect of GV and various metabolic and behavioral outcomes potentially associated with the interventions. At the end of this study, we will assess the acceptability and maintainability of the intervention through interviews.

**Clinical trial registration:**

Chinese Clinical Trial Registry, identifier ChiCTR2200058935.

## Introduction

The 2018 China National Survey reported that the prevalence of diabetes mellitus among adults aged 18 years and older in China was 12.4%, and estimated that the number of adults with diabetes has reached 114 million, with China having the largest number of people with diabetics worldwide. Furthermore, 38.1% of people are prediabetic, indicating that a large number of people are at high risk of the future development of type 2 diabetes (1). The glycemic profile of diabetes is characterized by chronic persistent hyperglycemia, hypoglycemia, and acute glycemic variabilit (GV). The hemoglobin A1c (HbA1c) has been commonly accepted as the gold standard for chronic persistent hyperglycemia, and reflects the average blood glucose status over the past 2–3 months (2). However, even in patients with similar HbA1c, within-day GV may be different (3). Observational studies with human populations and experimental studies with animals have found that GV is positively associated with diabetic retinopathy, which is an independent risk factor for cardiovascular autonomic neuropathy in patients with new-onset type 2 diabetes, increases all-cause mortality in critically ill patients, and has negative effects independent of chronic persistent hyperglycemia by activating oxidative stress, impairing endothelial cell function, and exacerbating inflammatory responses (4–8). The American Diabetes Association (ADA) 2020 Standards of Medical Care in Diabetes also include a Time in Range (TIR) >70% as one of the key indicators for glycemic management due to the strong correlation between temporal TIR and HbA1c in the range of GV indicators (9). Therefore, improving GV is important to delay the development of diabetes and its complications and to improve the prognosis and quality of patient survival.

GV is defined as both upward (postprandial) and downward (interprandial) acute variability of glucose around a mean value (10). Researchers have attempted to lower peaks and raise nadirs through various dietary interventions, such as changes in meal timing, meal order, carbohydrate quality, quantity, or distribution throughout the day; protein intake, dietary fiber intake and macronutrient ratios (11–14). Among these interventions, premeal snacking is the simplest intervention that has attracted attention as it does not require major changes to overall eating habits. Studies have attributed the benefits of premeal snacks to the second meal effect, which is defined as the effect of a prior meal on reducing postprandial glycemic excursions (15). A growing body of recent studies has used the “second meal effect” theory to intervene in blood glucose variability (16, 17). Many previous studies have focused on single nutrients as premeal interventions. It has been suggested that the use of an intervention with a small dose of whey protein before a meal is more effective than interventions that use soy protein for improving appetite, energy intake, and body composition (18). However, this finding is somewhat inconsistent with the results of an 11-year longitudinal study of the effects of different food sources of protein on metabolic syndrome, which concluded that a diet high in plant protein and low in animal protein helps prevent metabolic syndrome in healthy people (19). The results of a meta-analysis showed that fasting blood glucose, HbA1c, and fasting insulin levels were significantly reduced in patients with type 2 diabetes when the daily intake of soy products accounted for more than 35% of the total protein intake (20). In addition, nut consumption may reduce the risk of T2DM and cardiovascular disease (CVD) by improving glucolipid metabolism, maintaining body weight, and improving endothelial function (21). Several studies have found a significant effect of a nut-rich diet on glycemic control in patients with obesity or adults with type 2 diabetes (22–24). The long-term intake of almonds, which are widely accepted as snack, has been suggested to improve glycemic control and lipid profiles in patients with T2DM (25). Recent advances in appetite research also demonstrated the effectiveness of raw almond intake in healthy females (26). However, there is still a lack of randomized controlled trials addressing the effects of nuts as premeal snacks on GV.

In studies of the second meal effect, the meal pattern is also very important to the results. Most of the currently proposed premeal intervention studies are conducted under well-controlled laboratory conditions with uniformly balanced diets or use glucose tolerance tests to simulate eating behavior. Although the effects were obvious, it is not clear that similar benefits can be achieved under real daily diet conditions. Moreover, single nutrients or intervention foods in experimentally specific ratios are not readily available in daily life and are difficult to adapt to the different dietary habits of people in China and other regions, which may lead to poor adherence. Therefore, we will select easily accessible natural foods, i.e., soy powder, milk powder, and almonds, to represent high plant protein, high animal protein, and high fat premeal snacks intervention, respectively, and evaluated their effects on GV under two different dietary patterns: habitual diets and balanced standard meals. In this trial, we will fully consider dietary habits, offer common foods as premeal snacks without energy restrictions, and detect the effects on GV and energy intake. Our trial is expected to have high applicability, operability, and acceptability, which can provide evidence for further application in T2DM populations.

The primary aim of this study is to evaluate whether premeal snacks of natural foods improve GV and which kind of premeal snacks lead to better effects in prediabetic subjects. We hypothesize that plant-based high-protein snacks will lead to a non-inferiority effect of animal-based high-protein snacks on GV. The secondary objective is to evaluate whether these interventions have a positive effect on insulin, HOMA-IR (homeostasis model assessment for insulin resistance), HOMA-β (homeostasis model assessment for β cell function), C-peptide, body weight, waist circumference, abdominal circumference, subjective appetite, hunger, and satiety. Furthermore, we will assess the acceptability and maintainability of these interventions.

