### Test snacks

In the 3 premeal snack arms, all participants will be given prelunch snacks 30 min before lunch. Prelunch snacks will comprise soy powder and milk powder which will be completely dissolved in 250 ml of water, unsalted roast whole almonds snacks with 250 ml of water, while an equal amount of water (250 ml) will be given to subjects in the control group. The total calories of the three snacks will be similar to each other, from 80 to 90 kcal. This calorie selection was based on the minimum calories needed to relieve the symptoms of hypoglycemia (28). The specific composition of the three food items is shown in Table 3.

**Table 3 T3:** Macronutrient composition of the test snacks.

**Per serving**	**Soy powder**	**Milk powder**	**Almonds**
Weight(g)	18	25	13
Energy (kcal)	83	90	85
Carbohydrate (g, % of energy)	6.2 (30%)	14.0 (62%)	2.7 (12%)
Protein (g, % of energy)	7.2 (35%)	7.5 (33%)	2.7 (12%)
Fat (g, % of energy)	3.0 (32%)	0.38 (3%)	6.8 (72%)

*As an example for soy powder, in this trial, we used a total weight of 18 grams of soy powder as a pre-meal snack, which provided 83 kcal of total energy; of the 18 grams of soy flour, 6.2 g of carbohydrates provided 30% of the total energy, 7.2 g of protein provided 35% of the total energy, and 3.0 grams of lipids provided 32% of the total energy, respectively*.

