### Comparisons

First, the three intervention arms will be combined as a group and compared with the control group to evaluate whether the premeal intervention could improve GV. Second, the two arms with high-protein snacks will be combined as a group and compared with the control group; moreover, the high-fat snack arm will be compared with the control group to evaluate whether the two snacks (high-protein and high-fat snacks) could improve GV. If both the high-protein and high-fat snacks show significant improvement effects, we will further directly compare the high-protein snack (combining milk powder and soy powder into one group) with the high-fat snack (almonds) interventions to evaluate which is better. Third, we will also compare the milk powder group with the control group and the soy powder group with the control group, and if both high-protein snack groups show significant improvement, we will further compare the animal protein and plant protein groups directly to verify whether the plant protein group is similar to the animal protein group. Finally, we will compare all the results from different dietary patterns to determine whether premeal snacks have similar effects under habitual diet and standard balanced meals.

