In conclusion, this is the first RCT protocol that directly compares the effects of different natural snacks under different dietary patterns on GV. We will carry out a careful and rigorous research protocol for the following three issues we want to study: [1] the comparison of GV improvement effects between high-protein snacks and high-fat snacks; [2] the comparison of GV improvement effects between animal-based high-protein snacks and plant-based high-protein snacks; and [3] the comparison of the effects under two different dietary patterns. The limitation of this study is that we will use nuts eaten with water instead of nut powder solution. Because the high-fat powder solution does not have good compliance, we will consider the acceptability of the subjects. Therefore, there may be confounding factors caused by chewing activities in the whole nut group. In addition, the number of people included in this study will be quite small, so the conclusions should be extrapolated with more people. Another limitation of this study is the short duration of the experiment, with only 4 days per period. This is because the maximum validity of a single CGM device is only 14 days. Therefore, the effects we derive will represent only acute effects, and more long-term anthropometric and metabolic outcomes will need to be validated with longer-term experiments.

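### Soy versus milk is read as plant versus animal protein, but the two snacks differ mainly in carbohydrate and fat, so the result cannot be assigned to protein source

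*Protocol article*

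**What the plan says.** The Introduction gives each food a nutrient role: "soy powder, milk powder, and almonds, to represent high plant protein, high animal protein, and high fat premeal snacks intervention, respectively". It hypothesises that the plant-based high-protein snack is non-inferior to the animal-based one, and the Discussion repeats this for soy powder and milk powder.

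The Comparisons section uses the same roles. It would "directly compare the high-protein snack (combining milk powder and soy powder into one group) with the high-fat snack (almonds) interventions", provided both types first beat control. If soy and milk each beat control, those two arms are compared directly to "verify whether the plant protein group is similar to the animal protein group".

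The Test snacks section states what is matched: "The total calories of the three snacks will be similar to each other, from 80 to 90 kcal". Table 3 gives the composition. For soy its footnote says "6.2 g of carbohydrates provided 30% of the total energy"; the table puts soy protein at 7.2 g (35%) and soy fat at 3.0 g (32%). For milk the table gives 14.0 g carbohydrate (62% of energy), 7.5 g protein (33%) and 0.38 g fat (3%). For almonds it gives 2.7 g, 2.7 g and 6.8 g (12%, 12% and 72%).

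The closing limitations name chewing ("there may be confounding factors caused by chewing activities in the whole nut group"), the small sample and the short duration. They do not mention the macronutrient differences between the snacks.

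**The concern.** A contrast named after protein source should differ mainly in protein source. Here protein dose is well matched, but carbohydrate and fat are not, and the milk snack takes nearly twice as much energy from carbohydrate as from protein.

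This matters because every primary outcome is a glucose measure (MAGE, TIR, AUC, CV, MODD). The Introduction lists carbohydrate quantity and macronutrient ratios among the dietary levers researchers have tried on glycemic variability, and the Discussion says that variability changes with macronutrient ratios. The Continuous glucose monitoring section describes leaving out whole days only. Nothing in the article removes the half hour between snack and lunch, so the snack's own glucose effect enters the outcome.

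If soy and milk looked alike, soy's lower carbohydrate or higher fat could be offsetting a real difference in protein source. If they differed, protein source might have nothing to do with it. The documents do not say in which direction the extra carbohydrate would move MAGE, so no sign can be given to the distortion.

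**Working it through.** **Inputs** (Table 3, per serving)

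| | Soy | Milk | Almonds |
|---|---|---|---|
| Energy, kcal | 83 | 90 | 85 |
| Carbohydrate, g | 6.2 | 14.0 | 2.7 |
| Protein, g | 7.2 | 7.5 | 2.7 |
| Fat, g | 3.0 | 0.38 | 6.8 |

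Assumption: 4 kcal/g for carbohydrate and protein, 9 kcal/g for fat. The article does not state these factors.

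**Step 1. Reproduce the table's energy shares** (grams × factor ÷ stated kcal)

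- Soy: carbohydrate 24.8/83 = 29.9%, protein 28.8/83 = 34.7%, fat 27/83 = 32.5% (stated 30, 35, 32).
- Milk: carbohydrate 56/90 = 62.2%, protein 30/90 = 33.3%, fat 3.42/90 = 3.8% (stated 62, 33, 3).
- Almonds: carbohydrate and protein 10.8/85 = 12.7% each, fat 61.2/85 = 72.0% (stated 12, 12, 72).

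All agree to within one percentage point, so the table is sound and the factors are adequate.

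**Step 2. Soy versus milk**

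- Protein: 7.5 − 7.2 = 0.3 g, or 1.2 kcal.
- Carbohydrate: 14.0 − 6.2 = 7.8 g, or 31.2 kcal; ratio 14.0/6.2 = 2.26.
- Fat: 3.0 − 0.38 = 2.62 g, or 23.6 kcal; ratio 3.0/0.38 = 7.9.

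The largest energy difference is carbohydrate and the next is fat. The amount of protein barely differs.

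**Step 3. Pooled milk and soy versus almonds** (simple means, since allocation is equal)

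- Carbohydrate: (6.2 + 14.0)/2 = 10.1 g against 2.7 g; gap 7.4 g, 29.6 kcal.
- Protein: (7.2 + 7.5)/2 = 7.35 g against 2.7 g; gap 4.65 g, 18.6 kcal.
- Fat: (3.0 + 0.38)/2 = 1.69 g against 6.8 g; gap 5.11 g, 46.0 kcal.

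Fat, the labelled nutrient, is the largest gap in energy. Carbohydrate comes second, ahead of protein. By energy the pooled group is (24.8 + 56)/173 = 46.7% carbohydrate and (28.8 + 30)/173 = 34.0% protein.

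**Step 4. Can the analysis separate the components?** Every participant in an arm receives the same snack, so snack carbohydrate is constant within arm and fully determined by arm. No arm is matched to another on carbohydrate, and the water arm does not isolate it. Covariate adjustment cannot split the arm effect into a protein-source part and a carbohydrate or fat part.

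**The case against.** The use of whole foods is deliberate and reasoned. The Introduction sets aside single nutrients and specially formulated foods because they are hard to obtain and may harm adherence. Unequal macronutrients follow from using natural foods at similar energy, and Table 3 discloses them in full. The primary aim asks which kind of snack works better. The Discussion ties its labels to soy powder and milk powder and draws a food-level implication for people who are lactose intolerant. The Comparisons section already sets milk, soy and almonds each against water. All of this stands, and it limits the point to how results are labelled and interpreted.

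Three stronger readings are tempting but unsupported. A reader might infer that the closing aims on protein versus fat and on plant versus animal protein cannot be answered. They are worded in terms of snacks, and randomisation answers them food against food. A reader might infer that the pooled contrast fails in the same way as soy versus milk. It does not: its largest energy gap is the intended one, fat, and at similar energy less fat must mean more of something else. A reader might infer that the pooled comparison must lose its place. That is a matter of preference and does not follow from the imbalance.

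What the objection does not remove is the step from food to nutrient. The Comparisons section names plant and animal protein groups, the pooling rule rests on the protein label, and the limitations give chewing as the only confounder specific to a snack.

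**Conclusion.** The point holds as one of interpretation, firmly for soy versus milk. These arms differ by 7.8 g carbohydrate (milk 2.3 times soy) and 2.6 g fat, with only 0.3 g between them in protein, so no outcome of that comparison identifies protein source. It holds to a lesser degree for pooled milk and soy versus almonds, where a 7.4 g carbohydrate gap (about 30 kcal) accompanies the fat gap (about 46 kcal) and the protein gap (about 19 kcal). That contrast describes these snacks and not protein against fat as nutrients.

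The gram figures come straight from Table 3. The kcal figures rest on the 4/4/9 factors, and the pooled figures on equal arm sizes. The size and direction of any effect of the imbalance on MAGE are unknown. The food-level randomised comparisons are not in doubt.

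**What to change.** In the Introduction, Comparisons and Discussion, including its concluding paragraph:

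- State the hypothesis, contrasts and conclusions by food: soy powder versus milk powder, and these milk and soy snacks versus almonds.
- Say explicitly that effects cannot be assigned to protein source, or to protein versus fat.
- Add to the limitations, beside chewing, the soy-milk differences of 7.8 g carbohydrate and 2.6 g fat, and the 7.4 g carbohydrate difference between the pooled group and almonds.
- Keep the pooled comparison if wanted, reported together with the single-food results.

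The foods, arms, participants and data stay as they are. The cost is a narrower claim: about the snacks tested, not about plant versus animal protein in general.

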## Methods and analysis

### Study design

This study is a single-center, open-label, multiparallel group, randomized controlled trial. The study consists of two intervention periods: [1] under habitual diet conditions and [2] under balanced standard meal conditions. After a 3-day experiment run-in period, a total of 32 subjects (16 males and 16 females) will be randomized into one of 4 arms in 1:1:1:1 ratio (Figure 1). The 4 arms will include soy powder and milk powder which will be completely dissolved in 250 ml water, almond snacks with 250 ml of water, and a control arm (250 ml of water). Test days will be scheduled before and after the two intervention periods to assess the potential effects of premeal snacks under the habitual diet and standard balanced diet patterns, respectively. During the entire period of this experiment, subjects will be asked to complete a food recording diary (online) including the type, amount, and time of all meals, snacks, and drinks except water (in the form of photos and text). Physical activity and sleep will also be recorded via a mobile app for step count and sleep time records. The study will be performed at Wenzhou Medical University. The protocol followed the Standard Protocol Items: Recommendations for Interventional Trials statement (27).

**Figure 1 F1:**
[figure not shown]
Study design. *Data from CGM are excluded from the final analysis. CGM, continuous glucose monitoring.

### Participant recruitment and screening

Pre-diabetic females and males aged 18–60 years were screened for eligibility according to the inclusion and exclusion criteria, which are listed below in Table 1. Prediabetes was defined as impaired fasting glucose (IFG) and/or impaired glucose tolerance (IGT) and/or an HbA1c of 5.7–6.4%. Subjects were recruited through bulletin board posters and social media advertisements. We sent detailed information by e-mail to anyone interested in this study by e-mail. Prescreening was conducted by questionnaire through personal telephone interviews, in which we recorded age, sex, ethnicity, dietary habits, biological rhythms, sleep, physical activity, family history, etc. If he or she decided to participate in the study, the volunteer signed the written informed consent form, and they were invited to undergo a face-to-face screening at Visit 0 (V0). At V0, subjects underwent a health screening and an oral glucose tolerance test (OGTT). Subjects were informed that their participation is voluntary and that they may withdraw their consent at any time.

**Table 1 T1:** Eligibility criteria.

**Inclusion criteria**
• Aged from 18 to 60 years • FBG 6.1–6.9 mmol/L (IFG) OR 2 h PG (75 g OGTT) 7.8–11.0 mmol/L (IGT) OR HbA1c 5.7–6.4% • Stable bodyweight (changes <5 kg) in the past 3 months • Consumes 3 meals (breakfast, lunch, and dinner) a day at regular time points • Similar levels of physical activity (light manual worker)
**Exclusion criteria**
• Metabolic diseases, including but not limited to diabetes mellitus, cardiovascular disease, kidney or liver disease, hypertension, or hyperuricemia • Special diet requirements, such as vegetarian, or Muslim diets • Treatment with medication that significantly affects glucose metabolism, appetite, or energy balance in the past 3 months • Pregnancy or breastfeeding • Acute or chronic food allergies • Diagnosed or self-reported gastrointestinal disease or discomfort • Shift work or night shift work • Continuous or accumulated smoking for more than 6 months • Daily alcohol drinking
